### Data extraction methods

Healthcare providers will routinely and continuously enter data in the eRegistry during patient care, and all outcomes are informed by secondary data. Anonymous data will be extracted from the eRegistry in accordance with the standard operating procedure (SOP) of the Palestinian maternal and child health eRegistry for routine registry operations and use of data for research purposes.

### Data management

The data in the eRegistry will be managed in accordance with the governance structure approved by the Palestinian MoH. Only pre-defined anonymous data needed for the outcomes will be extracted from the eRegistry by PNIPH staff for this trial. The pre-defined anonymous original dataset will be provided to the trial sponsors and to our independent trial monitors (CISMAC), for independent monitoring and safeguarding.

### Statistical methods

Intention-to-treat analysis will be performed for the primary outcomes to compare each independent intervention arms (QID, TCC, and QID and TCC) with the control, using individual-level data taking the design effect of the clustering into account. Descriptive statistics will be reported, and appropriate tests will be used to compare variables between the groups. Statistical significance will be set at *p* < 0.05. Appropriate bivariate and multivariate regression analyses will be performed. The regression analyses will take the design effect of the clustering into account and enable adjustment for any relevant variables not accounted for during randomization. We will do complete case analyses and consider appropriate imputations for missing data. We will present cluster-wise effects of the intervention to explore whether a disproportionately large part of the effect can be ascribed to extreme effects in a few large clusters. The interaction effect of the two interventions will be performed as a secondary analysis. We will conduct per-protocol analyses in cases of protocol violations, including withdrawal of the eRegistry, and data from these clusters will be excluded from the time of violation when appropriate. Data will be analyzed using the latest version of STATA (Stata Statistical Software: College Station, TX: StataCorp LP).

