**Fig. 2 Fig2:**
[figure not shown]
Flow diagram showing eligible primary healthcare clinics (PHCs) and allocation

A total of 138 clusters (individual PHC and a combination of two PHCs served by the same healthcare provider for two clusters) were eligible for randomization. They enrolled a mean of 344 and a median of 131 new pregnant women in 2016 (Additional file 1). Data from all ANC visits occurring in the included PHCs during the study period will be used to assess our outcomes.

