### Sample size

Sample size calculations for the primary outcomes were performed in STATA “clustersampsi” (StataCorp. 2015. Stata Statistical Software: Release 14. College Station, TX: StataCorp LP). We estimated the minimum detectable difference for comparison of each intervention arm with the control arm without assuming the effect of multiple comparison (using a single control to each intervention arm). The control prevalence for the primary outcome, using data from the eRegQual CRCT, ranged from 30 to 85% for comparison I (QID vs control) and from 34 to 53% for comparison II (TCC vs control) (unpublished results). The 138 eligible clusters have an average of 172 new pregnancies per 6 months (ranging from 23 to 1500) and a 1.69 coefficient of variation of cluster size (2016 data). We assumed a priori intra-cluster correlation coefficient (ICC) of 0.05 and set the statistical significance level to 5%. We are 80% powered to detect an estimated relative 50% increase for the outcomes with the smallest control prevalence (e.g., improving anemia screening and management at 24–28 weeks’ gestation from 30 to 45%).

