### Allocation

Statisticians at the Center for Intervention Science in Maternal and Child Health (CISMAC), University of Bergen, Norway, performed the randomization independently without any influence from the research team.

PHCs were allocated to the TCC intervention, QID intervention, TCC and QID intervention, or control group with an equally 1:1:1:1 randomization ratio. The randomization was stratified by the point in time the eRegistry was implemented, and constrained on laboratory availability, ultrasound availability, and the size of the PHC.

In total, 10,000 randomization allocations were generated. The 10% best and balanced allocations with the least differences between the arms for the given covariates were identified, and one of these allocations were randomly selected for the trial [36].

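### The only stated adjustment rule names variables outside the randomisation, and nothing puts the stratification and constraint variables into the primary models

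*Protocol article*

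**What the plan says.** Two sections of the protocol article bear on this.

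**Allocation.** Clusters were allocated "with an equally 1:1:1:1 randomization ratio". On the stratification: "The randomization was stratified by the point in time the eRegistry was implemented". Within that, allocation was "constrained on laboratory availability, ultrasound availability, and the size of the PHC". The constraint works by selection from 10,000 generated allocations: "The 10% best and balanced allocations with the least differences between the arms for the given covariates were identified". One of these was then drawn at random.

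**Statistical methods.** Each intervention arm is compared with control on individual-level data, with clustering taken into account. The regressions will also "enable adjustment for any relevant variables not accounted for during randomization". This is the only statement about which covariates enter a model. No section says that the stratification variable or any of the three constraint variables does.

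**The concern.** When allocation is stratified or constrained on a clinic characteristic that predicts the outcome, chance differences between arms on that characteristic are largely removed. The treatment estimate then varies less from one possible allocation to another. A model without the characteristic does not recognise this: its variation stays in the residual between-clinic term and so in the reported standard error. Intervals come out too wide and the test rejects too rarely under the null. Including the design variables makes the reported precision match the way the trial was randomised.

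The stated rule points to the complementary set, as if balancing a variable at allocation removed the reason to model it. There is some ground in the article for expecting the design variables to matter. The primary outcomes include hemoglobin and blood glucose testing, and the Outcomes section widens some visit windows partly so that laboratory results can arrive and be recorded. At stake is precision. Neither bias nor false-positive control is threatened.

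**Working it through.** **Inputs from the article.** "A total of 138 clusters" in four equal arms, so 138/4 = 34.5 per arm. "The 138 eligible clusters have an average of 172 new pregnancies per 6 months", with coefficient of variation (CV) of cluster size 1.69, intra-cluster correlation (ICC) 0.05, significance level 5% (two-sided assumed), and 80% power for 30% against 45%.

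**Assumed.** R², the share of between-clinic variance explained by the four design variables. The article gives no value, so a range is shown.

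**Step 1: the plan's own figure.**
- Design effect = 1 + ((CV² + 1)·m − 1)·ICC = 1 + ((1.69² + 1)·172 − 1)·0.05 = 34.11.
- Effective number per arm = 34.5·172/34.11 = 174.0 (171.4 with 34 clusters, 176.5 with 35).
- Needed for 30% against 45% at 80% power: 163 per arm, or 176 with continuity correction.
- Without the correction, power is 0.82 to 0.83.

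The stated 80% reproduces. It assumes no gain from covariates.

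**Step 2: analytic limit at the plan's own target.** Assume the design balances the four variables perfectly. The true variance then follows an adjusted design effect of (1 − ICC) + (CV² + 1)·m·ICC·(1 − R²), while the unadjusted model still reports 34.11. For R² = 0.2:
- Adjusted design effect = 0.95 + 663.25·0.04 = 27.48.
- Ratio of standard errors = √(34.11/27.48) = 1.11.
- Type I error of the unadjusted test = 2·(1 − Φ(1.96·1.114)) = 0.029.

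| R² | SE unadjusted / adjusted | Type I error, unadjusted | Power 30% v 45%, unadjusted | Power, adjusted |
|---|---|---|---|---|
| 0 | 1.00 | 0.050 | 0.827 | 0.827 |
| 0.1 | 1.05 | 0.039 | 0.839 | 0.863 |
| 0.2 | 1.11 | 0.029 | 0.853 | 0.899 |
| 0.3 | 1.19 | 0.020 | 0.868 | 0.932 |
| 0.5 | 1.40 | 0.006 | 0.905 | 0.982 |

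Balance is never perfect, so these figures are a limit.

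**Step 3: simulation of the design.** The set-up was 138 clusters, four arms, two strata, and allocation drawn from the best 10% of 2,000 candidates. Cluster sizes were log-normal, truncated to 23–1500. The control rate was 30%, ICC 0.05, and effects linear. Each setting had 2,000 trials, analysed by weighted cluster-level regression with and without the four variables. A 7-point effect was chosen to keep power off its ceiling.

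| R² | Model | Mean reported SE | True SD | Type I error | Power, 7 points |
|---|---|---|---|---|---|
| 0 | unadjusted | 0.0276 | 0.0277 | 0.047 | 0.687 |
| 0 | adjusted | 0.0279 | 0.0279 | 0.046 | 0.676 |
| 0.2 | unadjusted | 0.0276 | 0.0259 | 0.036 | 0.716 |
| 0.2 | adjusted | 0.0255 | 0.0255 | 0.052 | 0.767 |
| 0.4 | unadjusted | 0.0276 | 0.0235 | 0.023 | 0.731 |
| 0.4 | adjusted | 0.0229 | 0.0226 | 0.048 | 0.843 |

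SE and SD columns are from the null runs. The unadjusted SE exceeds the true SD by a factor of 0.0276/0.0259 = 1.07 at R² = 0.2 and 0.0276/0.0235 = 1.17 at R² = 0.4. Monte Carlo error on a 5% rejection rate is √(0.05·0.95/2000) ≈ 0.005, so the fall to 0.036 and 0.023 is not simulation noise.

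**The case against.** The best defence is that the clause permits adjustment and forbids none. It can be read as saying that the randomisation variables are already handled and others may be added. A journal article also leaves the full covariate list to a statistical analysis plan, which is not shown. Both points stand as far as they go. A reader might infer that the plan excludes the design variables, and the text does not say that. But the point here is not a missing list: the article does state a rule, and the rule names the wrong set.

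A reader might also infer that significance tests between groups will choose the covariates, because Statistical methods mentions such tests shortly before the adjustment clause. Nothing connects the two sentences. The Blinding section also withholds the allocation codes until the analyses are complete. That inference is unsupported and forms no part of this point.

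On size, three objections stand. The values of R² are assumptions. The 7-point effect is smaller than the 15-point difference in the sample size example. And the simulation weights cluster-level results, whereas the plan analyses individual-level data. The plan's design effect implies a standard error near √(2·0.3·0.7/174) = 0.049, against 0.028 in the simulation, so the simulated power figures do not carry over directly. They show direction and rough scale.

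**Conclusion.** The point holds as a correction to the stated adjustment rule. Followed as written, the primary models would leave out implementation time, laboratory availability, ultrasound availability and clinic size. If these predict the outcomes, the standard errors are too large and the test is conservative. With 20% or 40% of between-clinic variance explained, the simulated type I error is about 3.6% or 2.3%, and about 5 or 11 percentage points of power are forgone for an assumed 7-point effect. With nothing explained, no material difference appears.

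Two stronger readings are tempting and fail. The omission does not inflate type I error; it lowers it. Nor does it undermine the stated 80% power: that figure assumes no covariate gain, and unadjusted power at 30% against 45% stays at or above 0.827 over the range examined. The loss is relative to what the same data could deliver with adjustment.

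**What to change.** In Statistical methods, replace the clause "enable adjustment for any relevant variables not accounted for during randomization" with a statement that every primary model includes four covariates: implementation stratum, laboratory availability, ultrasound availability and clinic size (for example, log of 2016 enrolments). Name any other covariates in advance, as additional to these. If the unseen analysis plan already does this, bring the article's wording into line with it.

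The cost is small. The four variables were used at allocation, so they are already held for every cluster. Since Data management limits extraction to pre-defined items, they may need a line in the extraction specification. The statistical price is a few cluster-level degrees of freedom. A two-arm comparison has about 2·34.5 = 69 clusters, so with one parameter per variable the residual degrees of freedom fall from 67 to 63, or a little further if there are more than two strata.

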## Data monitoring

Data management and monitoring will be done in accordance with the SOP of the Palestinian maternal and child health eRegistry for routine registry operations. We have not designated a Data and Safety Monitoring Committee, due to the lack of potential significant harm, nor an Endpoint Adjudication Committee, since we will not use any subjective clinical data for outcome measures.

### Harms

This CRCT only utilizes the moment of opportunity of an ongoing implementation to study new digital interventions in a health systems approach. No potential for clinically significant harm has been identified during the development and implementation of this trial. Potential discomfort from worries may occur among women attending ANC in clusters receiving the TCC intervention, and this will be examined in a sub-sample (Fig. 1).

### Confidentiality

Data confidentiality will be handled in accordance with the Palestinian MoH’s legal framework for maternal and child health electronic registries. This CRCT will only utilize anonymous data to enable the assessment of the effectiveness of the interventions. We will publish only aggregate data, and no data on individual clients, care providers, or identifiable clusters will be published.

### Access to data

The data in the eRegistry belong to the Palestinian MoH, and the researchers will not have access to the entire registry or identifiable data of any kind. We will not publish the full data set as our legal rights to the data is limited to this analysis, and the richness of data would allow for several other analyses for which there is no ethics approval or approval from the Palestinian MoH. We will, however, publish syntaxes needed to recreate the data set from the eRegistry.

### Dissemination plan

This protocol follows the Standard Protocol Items: Recommendations for Intervention trials (SPIRIT) guidelines. A formal revision of the protocol will be done if the change can affect the study’s nature. The sponsors and our independent trial monitors (CISMAC) will have to agree on the revision, which will require renewed approvals from both the ethic committee in Norway and in Palestine, and the Palestinian health authorities. We will inform all users and stakeholders and publish the results of the CRCT in peer-reviewed open-access journals according to the Consolidating Standards of Reporting Trials (CONSORT) guidelines and the mHealth Evidence Reporting and Assessment (mERA) checklist. Results will also be presented at scientific meetings and congresses and to the Palestinian MoH directly. With permission from the MoH, we will inform all participating PHC and their staff directly. We will acknowledge any change in the study outcomes, study design, sample sizes, or significant administrative aspects that will impact the study’s nature when disseminating the findings. Authorship will be in line with the recommendations of the International Committee of Medical Journal Editors. Summaries of the results and other relevant information will be published on the eRegistries website.

## Discussion

We have designed a multi-arm CRCT with two digital health interventions, namely the QID for healthcare providers and TCC sent via SMS to pregnant women. The eRegistry employs the collection and use of systematic, uniform, and longitudinally entered routine clinical data, in algorithms that instantly drive these digital health interventions [5]. The QID and TCC interventions’ can impact the quality of the ANC service and the utilization of care by the pregnant woman, and the eRegCom CRCT aims to estimate the effectiveness.

Routine data from the eRegistry in Palestine demonstrates that both quality of care and utilization of care have significant room for improvement, and both need to be addressed to achieve a high effective coverage. To ensure healthy lives and promote well-being for all at all ages (Sustainable Development Goal 3), data and digital health are highlighted as accelerators [37]. Our interventions directly address the traditional lack of available clinical data in a timely manner from routine health information system to healthcare providers and clients in low- and middle-income countries [38], and the trial is a direct response to the WHO review group on digital health interventions’ request for effectiveness studies [19].

We used the Principles for Digital Development [39] and a human-centered design approach [40] to develop the eRegistry, and also the QID and TCC interventions. The Palestinian MoH and PNIPH have been heavily involved in all stages of the CRCT and led the communication towards healthcare providers. We will, in addition, assess the effect of the TCC intervention on women’s worries in pregnancy and their perceptions of ANC, to ensure that we do not introduce harm. Also, the unintentional exacerbation of inequities based on owning versus having access to a mobile phone will be explored. We do not have data to explore inequities towards those that do not own or have access to a mobile phone, but acknowledge this issue.

Our experience from the pilot data collection and a recent time-motion study [41] is that women are willing to participate, and we expect a high response rate in the assessment of women’s worries and perception of ANC. We anticipate to follow a comprehensive sample of women throughout ANC due to Palestinian’s restrictions on movement. Our large sample of PHCs, with no individual-level eligibility criteria, is representative for Palestine and presumably also for other settings with a similar organizational structure.

One or two healthcare providers per PHC is the most common organizational structure in Palestine, but some healthcare providers may work or be relievers in more than one clinic. Healthcare providers working in both TCC intervention and control PHCs will receive the TCC training, but they can only register women to receive text messages from the TCC intervention PHC. Healthcare providers working in both QID intervention and control PHCs will not receive the QID training, and therefore not the full intervention. This is to avoid contamination, as the action needed to improve care can be done from any PHC without the QID tool itself. Even though very few PHCs in the trial are operated by the same healthcare provider, this may potentially lead to an underestimation of the effectiveness.

Other limitations of this trial include the cadres of healthcare professions we target, which is only nurses, midwives, and community health workers. We exclude doctors, due to the risk of contamination as they work in several PHCs. However, we acknowledge that doctors play a significant role in the care for pregnant women. Our outcomes are dependent on the completeness of documentation by the healthcare provider, as our data source, the eRegistry, is the routine governmental documentation tool with few required data points. In order for the clusters to have comparable opportunities to succeed or fail, when it comes to management, we only include the first step in the management algorithm for our primary outcomes. For example, women with mild and moderate anemia, a new hemoglobin result after 4 weeks, will be counted as a success, without taking into account the response to that result. However, we will assess the total management chain in the secondary analysis.

We work closely with the Palestinian MoH to mitigate the risk of changes to the PHCs’ activities and staff during the trial. A key aspect of the work with eRegistries is to facilitate the uptake of the evidence-based findings in other countries and promote our digital interventions as “Global Public Goods” [29]. The eRegistry does involve high start-up costs, but once implemented, the intervention only requires moderate additional investments. We are in the midst of a digital revolution, and more than 68 countries are using DHIS2 [28], the eRegistry’s platform. The added value of the digital interventions can add value to investments in eRegistries.

## Trial status

The CRCT began recruiting on 1 December 2019, and we expect to reach the target sample size after 6 months, approximately 1 June 2020. Protocol version 2—April 2020.

## Data Availability

Not applicable.

## Abbreviations

ANC: Antenatal Care
CISMAC: Center for Intervention Science in Maternal and Child Health
CRCT: Cluster Randomized Controlled Trial
DHIS2: District Health Information Software 2
MCH: Maternal and Child Health
MoH: Ministry of Health
NGO: Non-Governmental Organizations
PHC: Primary Healthcare Clinic
PNIPH: Palestinian National Institute of Public Health
PPC: Postpartum Care
QID: Quality Improvement Dashboard
SOP: Standard Operating Procedure
TCC: Targeted Client Communication
